### Cost and cost-effectiveness evaluation

We will conduct a cost-utility analysis comparing the *Pharmacist* and *Pharmacist+HP* conditions, following the guidelines for conducting pharmacoeconomic analyses issued by the Panel on Cost-Effectiveness and Medicine and the International Society for Pharmacoeconomics and Outcomes Research [59-61]. We will conduct the analysis from the *health-system perspective*, taking into account *direct program costs and direct non-program costs.* Direct program costs will include personnel, educational materials, and any visit-related costs. Direct non-program costs will include cost for all major health care utilization for hospital admissions, emergency room visits, outpatient visits and prescription medications during the intervention period. Participants will complete an interview regarding healthcare utilization outside of UIMC during scheduled data collections including emergency room visits and hospitalizations. For health care use received at UIMC, hospital electronic records and billing data for enrolled participants will be used to identify ambulatory and hospital use, professional and technical visit fees, emergency room visits, as well as laboratory and other ancillary services use. Cost estimates for the program costs (salaries for HPs, etc.) will be based on prevailing costs from appropriate published national sources, where possible. For example, healthcare use costs will be estimated using national Medicare reimbursement rates (average DRG rates) for hospitalization, Medicare fee schedules for physician and other professional services, and Medicare’s Resource-Based Relative Value Scale (RBRVS) for outpatient procedures. Since our study will span a time period exceeding one year, costs will be discounted using a rate of 5% per year.

Our effectiveness measures will include improvements in A1c, blood pressure, cholesterol levels and projected quality-adjusted life-years (QALYs). The incremental cost-effectiveness ratio (e.g., cost per change in A1c) of *Pharmacist+HP* vs. *Pharmacist* alone will be estimated at the end of 12 and 24 months. Cost per QALY will be determined from projections of continued *Pharmacist+HP* involvement and assumptions concerning the continued effects of *Pharmacist+HP* on outcomes over time. The QALY and utility estimates will be based on a Markov model (CDC Diabetes Cost-effectiveness Group) [62]. Sensitivity analyses will estimate the impact of changes in factors such as age, induced health-care visits, incidence of complications, HP costs, physician time, and discount rates.

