**Methods/Design:**

The primary aim of this randomized trial is to evaluate the effectiveness of clinical pharmacists and HPs on diabetes behaviors (including healthy eating, physical activity, and medication adherence), hemoglobin A1c, blood pressure, and LDL-cholesterol levels. A total of 300 minority patients with uncontrolled diabetes from the University of Illinois Medical Center ambulatory network in Chicago will be randomized to either pharmacist management alone, or pharmacist management plus HP support. After one year, the pharmacist-only group will be intensified by the addition of HP support and maintenance will be assessed by phasing out HP support from the pharmacist plus HP group (crossover design). Outcomes will be evaluated at baseline, 6, 12, and 24 months. In addition, program and healthcare utilization data will be incorporated into cost and cost-effectiveness evaluations of pharmacist management with and without HP support.

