**Figure 1 F1:**
[figure not shown]
**Study Design.** The proposed study is a randomized trial with crossover after one year. Three hundred African-American and Latino patients with uncontrolled type 2 diabetes will be randomized to receive either *Pharmacist* or *Pharmacist+HP* conditions. After one year, groups will crossover. The *Pharmacist* group will be intensified by adding health promoter support. Concurrently, maintenance will be evaluated in the *Pharmacist+HP* group by phasing out health promoter support.

After one year, groups will crossover. The *Pharmacist* group will be intensified by adding health promoter support. Concurrently, maintenance will be evaluated in the *Pharmacist+HP* group by phasing out health promoter support. Outcomes in terms of medication adherence, A1c, blood pressure, and LDL-cholesterol levels will be evaluated at 0, 6-, 12- and 24-months.

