### Identification, recruitment, and randomization of participants

The recruitment process will be carried out separately for each ambulatory site as determined by the project coordinator and clinical staff. On-site research assistants (RAs) will receive referrals from staff or patients interested in being screened for the study. All participant medical records are reviewed by a study physician to ensure A1c eligibility. Individuals deemed eligible will be scheduled for an appointment at the university Clinical Interface Core facility to complete written consent, HIPAA authorization, and baseline data collection. The RAs will inform patients that the research is being conducted to improve medication management in diabetes care and to find out whether pharmacists and health promoters help people reach goals of therapy. The RAs will spend additional time discussing the study protocol in detail as part of consent procedures and use the “teach-back” method to ensure participant comprehension [30].

Randomization to receive either *Pharmacist* or *Pharmacist+HP* assignments for the first year will occur after consent and completion of all baseline data collection. A random sequence of 300 participant assignments will be used. Blocked randomization will ensure that allocation to experimental conditions will be balanced within four gender by ethnicity subgroups at each site. The project coordinator will independently determine group assignments and will log the information separately. Baseline results for A1c and fasting lipid profile are entered into the patient’s medical record by a study physician and electronically shared with the primary care physician and pharmacist.

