The primary analysis of each outcome in the repeated measures design will be conducted in a general linear mixed model framework. In addition, SPSS MANOVA (for repeated measures) will be used to explore the simultaneous impact of the treatment on multiple correlated dependent variables, including the use of Roy-Bargmann stepdown F-tests and discriminant function analysis as post hoc tests to identify subsets of outcome measures affected [35]. SPSS MIXED will be used to explore patterned covariance structures such as compound symmetry and autoregression along with incorporating time-varying covariates, such as depression. MANOVA secondary analyses will explore the impact on results of inhomogeneous baseline variables. Exploratory subgroup analyses will determine which participants in the intervention group had the greatest improvement in outcomes, based on demographic factors, health literacy, and medication regimen. Group by time-trend interaction contrasts also will be used to explore different group trajectories of change. In addition, we will investigate the potential consequences of medication intensification (e.g., initiation of insulin) by evaluating changes in body mass index and severe hypoglycemia.

We will explore diabetes-related behaviors (including eating habits, physical activity, and medication adherence) as well as medication treatment intensification as alternative mediators using MPlus [36]. We will also test the hypothesis that diabetes behaviors and clinical outcomes will be maintained one year after phase-out of HP support. Finally, we will test the hypothesis that diabetes behaviors and clinical outcomes improved by adding HP support after one year of *Pharmacist* alone.

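### The 24-month Pharmacist+HP versus Pharmacist cost-effectiveness ratio is taken a year after the arms cross over, so it contrasts earlier with later HP support and not the two named conditions

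*Protocol article*

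**What the plan says.** The section Cost and cost-effectiveness evaluation names one contrast for the incremental cost-effectiveness ratio, Pharmacist+HP against Pharmacist, and two times for it: the comparison with Pharmacist "alone will be estimated at the end of 12 and 24 months". It does not redefine the contrast for the later time.

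The randomised conditions last one year. Under Identification, recruitment, and randomization of participants, the "assignments for the first year will occur after consent and completion of all baseline data collection". The Figure 1 legend under Study design then states: "After one year, groups will crossover". The Pharmacist "group will be intensified by adding health promoter support", and maintenance is studied in the Pharmacist+HP "group by phasing out health promoter support". The Abstract agrees: "After one year, the pharmacist-only group will be intensified by the addition of HP support".

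Outcome "levels will be evaluated at 0, 6-, 12- and 24-months", so the last assessment falls a full year after the switch. For that second year, Data analyses sets out two hypotheses: that "diabetes behaviors and clinical outcomes will be maintained one year after phase-out of HP support", and that adding HP support after a year of pharmacist care brings improvement.

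**The concern.** One label covers two different contrasts. At 12 months the arms differ by a year of HP support, which is the comparison named. At 24 months each arm has had pharmacist care for two years and HP support for roughly one of them, in opposite order. Neither arm shows what two years of Pharmacist alone, or two years of Pharmacist+HP, would cost or achieve.

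Cost-effectiveness is a declared objective, and the Discussion describes HPs as contested in the US healthcare system. A 24-month ratio printed under the Pharmacist+HP versus Pharmacist label could be taken as the two-year value of HP support. It would instead reflect mainly the timing of that support, how well gains last and how well late-added support works.

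**Working it through.** The document gives no cost-effectiveness figure to reproduce. The check therefore follows the design through to the numerator and denominator of the ratio.

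**Inputs from the protocol article**
- Crossover at one year (Study design).
- Ratio at 12 and 24 months; costs discounted at 5% per year; programme costs include personnel; inpatient, emergency, outpatient and drug costs are also counted (Cost and cost-effectiveness evaluation).
- Planned A1c effect of 1.0 point, SD 1.8 (Sample size calculation; 1.0/1.8 = 0.56, as stated there).

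**Assumptions, not in the document**
- C, the cost of one HP-year, is the same in both arms. It stays as a multiplier.
- Year 1 is undiscounted and year 2 is divided by 1.05.
- The first-year gain from HP support is 1.0 point. A share r of it is retained at 24 months (0 to 1), and the late-added gain in the other arm is g (0.5 to 1.0 point).
- The effect in the ratio is the A1c difference at the visit.

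**HP exposure**

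| Time | Pharmacist+HP arm | Pharmacist arm |
|---|---|---|
| 12 months | 1 HP-year | 0 |
| 24 months | 1 HP-year plus any phase-out contact | 1 HP-year |

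**HP-programme part of the cost difference**
- At 12 months: C - 0 = 1.00C.
- At 24 months, no phase-out contact: C - C/1.05 = C(1 - 0.952) = 0.048C. Undiscounted it is 0.
- If phase-out uses a fraction p of an HP-year: 0.048C + 0.952pC. For p = 0.25 this is 0.048C + 0.238C = 0.286C.
- Had both conditions been kept for two years: C + C/1.05 = 1.95C.

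**A1c difference at 24 months** (positive favours the HP-first arm): D = r × 1.0 - g. The last column divides 0.048C by D, so it covers HP cost only.

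| Retained share r | Late gain g | D | HP cost per point |
|---|---|---|---|
| 1.0 | 0.5 | +0.5 | about 0.10C |
| 1.0 | 0.75 | +0.25 | about 0.19C |
| 1.0 | 1.0 | 0 | undefined |
| 0.5 | 0.5 | 0 | undefined |
| 0.5 | 1.0 | -0.5 | about -0.10C |
| 0 | 1.0 | -1.0 | about -0.05C |

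At 12 months the same quantity is 1.00C/1.0 = 1.00C per point. Even in the first row, where the ratio is finite and has the expected sign, its HP-cost part is about a tenth of the 12-month value, although HP support works in both arms. The change comes from the crossover and not from any change in what HP support costs.

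**The case against.** The best defence is that the economic section speaks of comparing conditions, and each group passes through both. Data analyses describes a crossover model with treatment, period and carry-over terms, so a 24-month estimate pooling both years could target the named contrast. It is true that the article does not spell out the computation, and that detail may properly sit elsewhere. But nothing links that model to the cost-effectiveness ratio. A pooled estimate would also need negligible carry-over, while the protocol hypothesises that gains persist after HP support is withdrawn. A comparison of year 2 alone does no better: its comparator would be patients who had just had a year of HP support.

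Other objections stand and limit the point:
- A reader might infer that the total cost difference at 24 months is close to zero. The document does not support that. The 0.05C figure covers HP cost only; other utilisation is counted and may differ between arms, and the phase-out schedule is not given.
- A reader might infer that the ratio must be undefined or have the wrong sign. That requires a late gain at least as large as the retained gain, and no passage says so. With a smaller late gain the ratio is finite and of the expected sign.
- A reader might infer that the cost-per-QALY result is compromised too. That result is a separate model projection which assumes that HP support continues, and nothing shows that it uses the 24-month arm difference.
- Immediate versus deferred support is a legitimate economic question, and maintenance and intensification are stated aims. The fault lies in the label and the contrast, not in having a 24-month analysis.

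**Conclusion.** The point holds for the 24-month ratio only. As planned, it carries the name of a comparison that the between-arm contrast at that time no longer makes. This is a mismatch between two things the article states, and not a missing detail.

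The fall in the HP-cost difference from C to about 0.05C rests on equal yearly HP cost, no phase-out contact and the stated discounting. The effect difference cannot be predicted from the document: over the range examined it runs from +0.5 to -1.0 A1c points, given a 1.0-point first-year gain. The supported conclusion is that the 24-month ratio may be finite, unstable, undefined or reversed, and in each case answers a different question from the one named. The 12-month ratio remains a valid estimate of the stated comparison, and the primary clinical comparison is not touched.

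**What to change.** In Cost and cost-effectiveness evaluation, limit the Pharmacist+HP versus Pharmacist ratio to the 12-month randomised comparison. Label any 24-month economic analysis *immediate versus deferred HP support*, and report the cost difference and the effect difference, each with an interval, alongside any ratio.

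This needs no new data and no change to the design. The price is giving up a 24-month ratio under its present label.

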## Discussion

To our knowledge, this will be the first study to evaluate the impact of HPs as a complement to clinical pharmacist management in a randomized trial. The study incorporates evidence-based procedures of clinical pharmacists and community HPs to assess their complementary involvement in diabetes management.

The study design includes clinic-based pharmacists. We chose to study pharmacists because the strongest empirical support for improved diabetes medication management currently lies in PCP-directed collaborative teams with pharmacists. In fact, collaborative medication therapy management by pharmacists has been approved in 46 states in the U.S. since 2008 for diabetes and dyslipidemia [63,64]. This growing level of pharmacist involvement supports the need for further study of pharmacists in team management as part of a patient-centered medical home [65].

To complement pharmacist efforts in reaching minority populations, we include HPs. Despite the endorsement of peer HPs by the American Association of Diabetes Educators (AADE) and American Public Health Association (APHA), they remain controversial in the U.S. healthcare system [66-68]. Criticisms of HPs focus upon the lack of formal evaluation studies supporting their effectiveness on clinical endpoints and weak connections between HPs and providers. This study may provide stronger evidence related to the benefits of HPs when they are closely connected to clinic-based pharmacists.

While a number of studies have examined the impact of HPs on diabetes management, there has been a greater emphasis on lifestyle modification than on medication management. Pharmacists provide a unique resource for HPs with their expertise in medication reconciliation, strategies to improve adherence, side effects, and prescription fill management. HPs may be less comfortable with the complexities of polypharmacy, adjustments of medication dosages, and the evolving nature of novel medication therapies utilized in diabetes care. This research will help in understanding the support that pharmacists may provide to community HPs. Important process data include the means by which pharmacists and HPs communicate (by telephone, in-person, or secure electronic mail).

A number of challenges and concerns have been considered. First, there may be significant variation in HP attention and impact. To address this, health promoters will be uniformly trained through a CDC-funded curriculum. We include regular re-evaluation of activities to detect drift. Health promoters will follow an established protocol for patient contact; and will maintain a log to be submitted to a supervisor for evaluation. Next, other health care providers, including PCPs, may adjust therapy independent of study procedures. Medical record reviews will describe medication changes if completed within the UIMC health care system (where it is expected to most commonly occur). Analyses will include medication changes by pharmacist or other provider. Finally, while a majority of Latino patients are Mexican-American in Chicago (~75%), others come from Puerto Rico or elsewhere, and may have a different cultural background. Health promoters are trained to be sensitive to these differences, in cases where there may be a mismatch between health promoter and client.

In conclusion, the study will evaluate an innovative, integrated approach to chronic disease self-management in minorities with poorly controlled diabetes. The approach is comprised of clinic-based pharmacists and community-based health promoters collaborating together. Pharmacists and HPs will target patient-level factors (i.e., lack of adherence to lifestyle modification and medications) and provider-level factors (i.e., clinical inertia) that contribute to poor clinical outcomes in diabetes. Importantly, the study design and analytic approach will help determine the differential and combined impact of adherence to lifestyle changes, medication, and intensification on clinical outcomes.

## Abbreviations

AADE: American Association of Diabetes Educators; APHA: American Public Health Association; BMI: Body Mass Index; DDS: Diabetes Distress Scale; DEEP: Diabetes Empowerment Education Program; DRG: Diagnosis Related Group; EMR: Electronic Medical Record; FQHC: Federally Qualified Health Centers; HIPAA: Health Insurance Portability and Accountability Act; HP: Health Promoter; ICC: Intraclass Correlation Coefficient; MTM: Medication Therapy Management; PCP: Primary Care Physician; PDC: Proportion of Days Covered; PCS: Perceived Competence Scale; QALY: Quality Adjusted Life Year; RA: Research Assistant; RBRVS: Resource-Based Relative Value Scale; SDSCA: Summary of Diabetes Self-Care Activities Measure; TSRQ: Treatment Self-Regulation Questionnaire; UIMC: University of Illinois Medical Center.
